**Figure 2 figure2:**
[figure not shown]
Simulated growth rate for the 6-Minute Walk Test (6MWT). SAVR: surgical aortic valve replacement; TAVR: transcatheter aortic valve replacement.

### Statistical Analysis

Data will be reported as median (interquartile range) values for continuous variables and as percentage (absolute number) values for qualitative variables. A Wilcoxon-Kruskal-Wallis test will be performed for continuous variables and Pearson chi-square tests for categorical ones.

A propensity score estimation will be provided to balance data in the SAVR and TAVR groups according to the baseline characteristics. A random forest classification algorithm [19] will be employed for propensity score computation.

A genetic algorithm [20] will be considered to match the data, taking into account the similarities in the estimated propensity scores. The algorithm automatically finds the set of matches, which minimizes the discrepancies between groups.

Once the data are matched, treatment groups will be compared to assess the quality of the matching procedure according to the baseline characteristics, reporting the same statistics as previously considered to describe patients receiving SAVR and TAVR.

Finally, a generalized estimating equations model [21] will be estimated on matched data to determine the time effect on the 6MWT performance in both treatment groups; the model will also include other confounding factors potentially affecting 6MWT.

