### Sample Size

The primary endpoint is represented by the potential gain—assessed through the 6MWT—in recovering physical function within the first 6 months after SAVR/TAVR. A sample size of 154 patients per group has been computed using a Kolmogorov-Smirnov test to evaluate the difference between the growth curves of 6MWT between the SAVR and TAVR groups. A simulation procedure has been performed assuming the following factors:

Logistic growth function for both groups.Mean growth rate of 10% for both samples, assuming a mean time (useful to recover a carrying capacity of 270 meters) of 100 days for SAVR and 80 days for TAVR (with a mean reduction of recovery time consisting of 20 days).A type I error probability equal to .05.Each scenario consists of a combination of sample sizes from 100 to 200, and a difference between midpoint time recovery ranges from 5 to 30 days.

A statistical power of 0.9 has been reached with a difference between a recovery time of 20 days for 150 patients. For each scenario, 100 simulations have been performed by sampling *n* growth curves (1 for each patient), assuming the following growth function: 
[figure not shown]

In this equation, α∼N (0.1,0.01), where α is the growth rate specifying the width of the sigmoidal curve; k is the carrying capacity; and β specifies the time when the curve reaches the midpoint of the growth trajectory.

The curves have been pooled computing the mean within the sample, obtaining a mean SAVR and TAVR growth rate, as shown in Figure 2. Total patients to be enrolled are 340 (170 in each of the SAVR and TAVR groups), considering a dropout rate of 10%.

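### Matching quality is to be judged with Wilcoxon and chi-square tests, which cannot flag an observed imbalance of about 0.2 SD at any attainable matched size

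*Protocol article*

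**What the plan says.** All of this stands in the Statistical Analysis section of the protocol article.

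- The descriptive set is defined first: "Data will be reported as median (interquartile range) values for continuous variables and as percentage (absolute number) values for qualitative variables". The tests follow: "A Wilcoxon-Kruskal-Wallis test will be performed for continuous variables and Pearson chi-square tests for categorical ones".
- A random forest propensity score and a genetic matching algorithm are then planned. Of the matching it says: "The algorithm automatically finds the set of matches, which minimizes the discrepancies between groups". The measure of discrepancy is not given.
- The balance check comes next: "Once the data are matched, treatment groups will be compared to assess the quality of the matching procedure according to the baseline characteristics". It is to be done by "reporting the same statistics as previously considered to describe patients receiving SAVR and TAVR".
- Last, a generalized estimating equations (GEE) model is fitted to the matched data, and "the model will also include other confounding factors potentially affecting 6MWT". These factors are not named.

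The section gives no standardised difference or other measure that is free of sample size. It also gives no rule for accepting balance and no expected number of matched pairs.

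**The concern.** The article fixes which statistics will judge the matching, and the only ones that formally compare the groups are significance tests. Whether a matched sample is balanced is a question about that sample, not a hypothesis about a population. A P value answers a different question, and its answer depends on the number of patients. If matching drops patients and the imbalance stays the same, the P value rises, so the check can seem to improve only because data were lost.

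Treatment here is chosen by heart-team indication, not by randomisation, so the SAVR and TAVR groups can be expected to differ at baseline. The balance check is the step meant to show whether matching has dealt with this. If it cannot see moderate differences in age, comorbidity or baseline 6MWT, they may remain in the matched 6MWT comparison without anyone being alerted.

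**Working it through.** **Inputs from the Sample Size section.** "A sample size of 154 patients per group has been computed using a Kolmogorov-Smirnov test". With 10% dropout the article enrols 170 per group, 340 in total. This figure reproduces as 154 × 1.1 = 169.4, rounded up to 170. (Dividing, 154 / 0.9, would give 172; nothing below depends on this.)

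**Assumptions.** Matching is 1:1 without replacement, so 170 pairs is the ceiling. The balance tests are two-sided at .05; the article states .05 only for the sample size. The smaller matched sizes below are illustrations.

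**Formulas.** For an observed standardised difference d with n per group, z = d / √(2/n). The smallest d that reaches P<.05 is 1.96 × √(2/n). For the Wilcoxon test, n is multiplied by its efficiency 3/π = 0.955 under normality.

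- At n = 170: √(2/170) = 0.1085, so the limit is 1.96 × 0.1085 = 0.213. For d = 0.2, z = 0.2 / 0.1085 = 1.84 and P = .065.
- At n = 154: √(2/154) = 0.1140, so the limit is 0.223. For d = 0.2, z = 1.76 and P = .079.

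| Pairs | Smallest d with P<.05 (normal) | Same, Wilcoxon | P if d = 0.20 | P if d = 0.25 | P if d = 0.30 |
|---|---|---|---|---|---|
| 170 | 0.213 | 0.218 | .065 | .021 | .006 |
| 154 | 0.223 | 0.229 | .079 | .028 | .008 |
| 120 | 0.253 | 0.259 | .121 | .053 | .020 |
| 100 | 0.277 | 0.284 | .157 | .077 | .034 |
| 75 | 0.320 | 0.328 | .221 | .126 | .066 |

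The P columns use the normal approximation. Read downwards, each shows the problem: a fixed imbalance of 0.25 SD is significant at 154 pairs and non-significant at 120, though nothing about the balance has changed.

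**Where each imbalance stops being flagged**, from n = 2 × (1.96/d)²:

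- d = 0.20: 2 × 9.8² = 192 pairs, above the 170 available, so it is never flagged.
- d = 0.25: 2 × 7.84² = 123 pairs (about 129 for Wilcoxon).
- d = 0.30: 2 × 6.53² = 85.4, so about 86 pairs (about 90 for Wilcoxon).

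**Categorical covariates behave alike.** Take 51/170 (30%) against 68/170 (40%). The standardised difference is 0.10 / √((0.21 + 0.24)/2) = 0.21. The chi-square test has standard error √(0.35 × 0.65 × 2/170) = 0.0517, so z = 1.93 and P = .053. A ten-point difference in a comorbidity is not flagged even with all patients matched.

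These figures concern observed differences. Power against a true imbalance would treat balance as a population hypothesis, which is the reasoning criticised here.

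**The case against.** The case on the other side has real weight.

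- **No acceptance rule is written.** A reader might infer that a matched set with P>.05 would be declared balanced. The article does not say so. Medians, interquartile ranges and percentages are reported beside the tests, and they do not drift with sample size as P values do. This stands: the most that can be said is that imbalance could pass unflagged. Still, the summaries come with no yardstick. For a normal covariate the interquartile range is 1.349 SD, so 0.2 SD is 0.2/1.349 = 0.15 of an interquartile range, which is easy to overlook.
- **The check is not the only safeguard.** A reader might infer that nothing else guards against confounding by indication. The same section plans a propensity score, matching that minimises discrepancies, and an outcome model with further confounders. This stands too. But the confounders are unnamed, and the article does not tie their choice to imbalances found after matching.
- **Imbalance of 0.3 SD is usually caught.** At 154 to 170 pairs it gives P = .008 to .006. It goes unflagged only below about 86 pairs, when roughly half of 170 per group has been lost, and the article gives no matched size. This limits the larger figures to a conditional statement.
- **Numerical limits belong in an analysis plan.** Agreed: the missing threshold is not the finding. The finding is the measure that the article does state.

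**Conclusion.** The point holds in a limited form. Significance tests are a poor measure of matching quality, and the article names no other formal comparative measure. Under 1:1 matching and a two-sided .05 reading, an observed imbalance of about 0.2 SD is non-significant at every attainable size; this needs no assumption about patients lost in matching. The larger figures, about 0.28 SD at 100 pairs and 0.32 SD at 75, hold only if matching discards that many.

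The resulting bias in metres walked cannot be derived. The article gives no SD for 6MWT, no slope of follow-up on baseline, and no target difference in metres: its sample size rests on a 20-day shift in recovery time. A reader might be tempted to express the imbalance as a share of a detectable 6MWT difference, but the document does not support any such figure.

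**What to change.** Name a measure of balance that does not depend on the number of pairs. Possible wording: *Balance will be assessed by the absolute standardised mean difference and the variance ratio of each baseline covariate, baseline 6MWT included, before and after matching. Covariates with an absolute standardised difference of 0.1 or more after matching will prompt re-tuning of the matching or will be included in the GEE model.*

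The planned medians, percentages and tests may stay beside these measures, provided that the tests are not used to judge balance. The limit of 0.1 is an example; what matters is to fix a limit before the matched outcomes are examined. Re-tuning should use baseline data only.

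The cost is one sentence of analysis text and one table column, with no new data. In a small matched set some covariates may miss the limit, which is why the wording says what happens then. Enrolment was still under way when the article was published, so the change could be made before analysis.

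### The GEE named for the 6MWT is not generally valid if missed tests depend on earlier walking distance; unequal loss of that kind between SAVR and TAVR could bias the 6-month contrast

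*Protocol article*

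**What the plan says.** The Sample Size section defines the primary endpoint as the gain on the 6MWT "in recovering physical function within the first 6 months after SAVR/TAVR". Tests are scheduled at baseline and at 1, 3, 6 and 12 months.

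The Statistical Analysis section matches SAVR and TAVR patients on baseline characteristics. It then states that "a generalized estimating equations model [21] will be estimated on matched data" to estimate how the 6MWT changes over time in each group, and adds that "the model will also include other confounding factors potentially affecting 6MWT". The confounders are not named. The section gives no weighting, imputation or working correlation, and rules none of them out.

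Loss appears once, in the Sample Size section: "Total patients to be enrolled are 340 (170 in each of the SAVR and TAVR groups"), reached "considering a dropout rate of 10" percent. This is one rate for both groups, used only to enlarge the sample.

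**The concern.** A GEE fitted to the available visits allows missingness to depend on covariates in a correctly specified mean model, procedure included. In general it does not allow missingness to depend on earlier outcomes that the model does not condition on. A likelihood model with the right mean and covariance does allow this.

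The 6MWT can be measured only in someone who attends and walks. Patients are 75 to 90 years old with severe symptomatic stenosis, so it is plausible that a poor early walker is likelier to miss a later test. The Introduction suggests faster recovery after TAVR, and the sample size assumes recovery 20 days sooner. Walking ability may therefore differ by procedure during follow-up, and walking-related loss may differ with it.

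The group that loses more of its weak walkers would then look better than it is. Matching works on baseline characteristics and cannot correct selection that arises after the procedure.

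**Working it through.** **The plan's own figure.** "A sample size of 154 patients per group has been computed using a Kolmogorov-Smirnov test". Adding 10% gives 154 × 1.1 = 169.4, so 170 per group and 340 in total, as printed. (Dividing instead, 154 / 0.9 = 171.1, gives 172 and 344.) The 10% therefore enters only the sample size.

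**Assumed inputs, not in the documents.** 6MWT SD 100 m; correlation between visits 0.5 to 0.7; true 6-month difference 0; overall loss 10%, split 15% versus 5% or 12% versus 8%; log-odds of a missed 6-month test rising by 1 for each SD of worse 1-month walking.

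**Independence working correlation.** With a treatment-by-visit mean and no further covariates, the GEE estimate at 6 months is the difference in means among those tested. Let z be the standardised 1-month value, m(z) the probability of a missed test, d its average and ρ the correlation between the 1- and 6-month values. For normal z and a logistic slope of 1:

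- mean of z among those tested = E[m(1 − m)] / (1 − d)
- shift in the observed 6-month mean = ρ × SD × that value

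| Loss d | E[m(1 − m)] | Mean z among tested |
|---|---|---|
| 5% | 0.0448 | 0.0448 / 0.95 = 0.047 |
| 8% | 0.0677 | 0.0677 / 0.92 = 0.074 |
| 12% | 0.0948 | 0.0948 / 0.88 = 0.108 |
| 15% | 0.1127 | 0.1127 / 0.85 = 0.133 |

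- 15% versus 5%: gap 0.133 − 0.047 = 0.086 (0.0855 before rounding). Bias 0.0855 × 100 × 0.5 = 4.3 m, to 0.0855 × 100 × 0.7 = 6.0 m. A log-odds slope of 1.25 gives 5.0 to 7.0 m. Hence about 4 to 7 m.
- 12% versus 8%: gap 0.034. Bias 0.034 × 50 = 1.7 m to 0.034 × 70 = 2.4 m.
- Equal loss by the same mechanism: gap 0, bias 0.

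The bias favours the group with more loss.

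**Exchangeable working correlation.** Large simulations under the same assumptions gave a bias of about 1 m or less at 15% versus 5%, and up to about 1.5 m when the true correlation was autoregressive. The likelihood model was within about 0.7 m of the truth, which is simulation error.

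**GEEs fitted at the planned size.** 154 per group, visits at 0, 1, 3 and 6 months, assumed SD 80 m, correlation 0.6, 200 replicates, Monte Carlo SE about 0.7 m. Bias in metres, independence / exchangeable:

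| Missed 6-month test depends on | 15% vs 5% | 25% vs 10% |
|---|---|---|
| procedure only | +0.1 / +0.5 | −1.0 / +0.3 |
| previous 6MWT (observed) | −3.5 / +1.0 | −6.3 / −0.1 |
| current 6MWT (unobserved) | −7.2 / −4.4 | −10.1 / −4.5 |

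With 10% loss in both groups, bias was −0.8 to +0.3 m in every setting. In the worst cell (unobserved value, 25% versus 10%), 95% interval coverage was 0.79 with independence and 0.90 with exchangeable.

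**Scale.** With 170 × 0.85 = 144.5 and 170 × 0.95 = 161.5 tested, the unadjusted SE is 100 × √(1/144.5 + 1/161.5) = 11.5 m, so 4 to 7 m is roughly 0.4 to 0.6 SE. The growth equation is not shown. Taking it as 270 / (1 + exp(−0.1(t − β))) with β of 100 and 80 days, the planned difference is 197.4 − 72.6 = 124.8 m at day 90 and 269.99 − 269.91 = 0.08 m at day 180. The bias is small beside the former and larger than the latter.

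**The case against.** The strongest reply is that the article names a GEE in one sentence and leaves the rest open. Nothing in it says the GEE is unweighted; a weighted GEE, or a GEE after multiple imputation, fits the wording. Missing-data rules are commonly left to the full protocol or analysis plan, neither of which is shown. That stands: the absence of those rules is no finding. What remains is that the estimator the article does name gives no general protection against the loss the article expects.

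A reader might infer three stronger claims that the documents do not support:

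- *The GEE is valid only if tests are missing completely at random.* This is too strict. Loss that depends on procedure or on other covariates in a correct mean model is allowed, and loss by procedure alone produced no material bias above. If the unnamed confounders include baseline 6MWT, the independence figure also falls: with equal correlation ρ between all visits it is about 0.0855 × 100 × (ρ − ρ²), or 2.1 m at ρ = 0.5 and 1.8 m at ρ = 0.7.
- *Loss will differ by procedure.* No section gives death, dropout or inability to walk by group. The Study Population section excludes life expectancy under 1 year and users of walking aids, which limits the mechanism at entry.
- *A mixed model cures the problem.* It does so only for loss explained by observed data. It does not resolve death, or loss driven by the current unseen value.

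It is also fair to say that an exchangeable working correlation removes most of the bias when loss follows earlier walking distance. The article does not commit to one.

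**Conclusion.** The point holds as a conditional risk, worth settling before outcomes are analysed. Bias needs two things together: missed tests related to walking ability beyond the model's covariates, and a difference in that loss between SAVR and TAVR. If both hold at 15% versus 5%, the 6-month contrast moves by about 4 to 7 m under independence and about 1 m or less under exchangeable correlation. At 12% versus 8% the independence figure is about 2 m, and with equal loss it is negligible. SD, correlation, slope and group-specific loss are all assumed, so neither the size nor the direction in this study can be read from the documents.

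**What to change.** Make the primary 6MWT analysis a likelihood-based repeated-measures model: treatment by categorical visit, unstructured covariance, baseline 6MWT as covariate, standard errors clustered on the matched pair. Alternatively, keep the GEE and weight each visit by the inverse probability of being observed, given earlier 6MWT and procedure.

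Under either choice:

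- add a sensitivity analysis for loss that depends on the unobserved value;
- handle death and inability to walk separately, for example in a ranked composite, because neither model resolves them.

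The cost is analysis wording, modest extra programming, and recording why each test was missed. The last is a data-collection item, so it should be settled early; the Results section reports 20 patients enrolled of the planned 340 as of October 2020.

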It is worth pointing out that there is a lack of specific data on the trajectories of physical recovery in patients receiving SAVR and TAVR, despite their widely acknowledged key roles in affecting postoperative outcomes, especially among elderly who are more prone to develop postoperative complications. Given the close relationship of physical activity with the outcomes of cardiac procedures, there is a growing interest in improving assessment of physical activity. Undoubtedly, several methods are available to assess physical function (and are widely used in both everyday clinical practice and clinical research) [15]. However, such approaches present several limitations, and the main one is that physical function is self-reported (and self-rated) by the patient. Self-reporting can be biased (eg, recall and desirability biases), and this might pose a barrier to further improvement in patients' recovery from surgery. In the last few decades, several tools have been developed to measure physical function objectively. Particularly, commercially available wearable technologies are increasingly used for both collecting and promoting patients' activity [16] in the health care setting. A recent review in the field has shown a broad spectrum of applications of such technologies for several purposes, including health promotion, health maintenance, and clinical monitoring of patients with various pathological conditions or patients undergoing surgery [17]. The fact that such devices allow for continuous data collection presents a promising opportunity to improve the monitoring of patients, especially those with chronic diseases, allowing for early detection of changes in patients' activity that need to be investigated by the clinicians [18]. However, the use of such devices has not been well established in everyday clinical practice.

This study aims to describe baseline (preoperative) physical function and to assess and compare 6-month postoperative changes in the physical function of patients undergoing treatment for aortic stenosis with either SAVR or TAVR with Edwards valve implants. It also aims to evaluate the feasibility of wearable devices in assessing physical function in such patients.

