Using wearable devices for the real-time monitoring of lifestyle habits and clinical parameters of patients undergoing cardiac surgery can present a promising opportunity for improving the clinical management and consequently, the health outcomes of such patients. Furthermore, information gained from this study can be helpful in providing patients contemplating intervention for aortic stenosis with practical counseling on expected changes in their functional status months after surgery.

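### The 6MWT recovery curve in each group is modelled only on matched patients, so at least one curve will not represent everyone who receives that procedure

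*Protocol article*

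**What the plan says.** The objective in the Protocol article (Introduction, and in similar words in the Abstract) is "to assess and compare 6-month postoperative changes in the physical function of patients undergoing treatment for aortic stenosis with either" SAVR or TAVR. It therefore covers the change in each group as well as the difference between groups. The Introduction gives as motivation that "there is a lack of specific data on the trajectories of physical recovery in patients receiving SAVR and TAVR". The Discussion adds that the results may support "practical counseling on expected changes in their functional status months after surgery".

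Under Statistical Analysis, a random-forest propensity score feeds a genetic matching algorithm: "The algorithm automatically finds the set of matches, which minimizes the discrepancies between groups". No matching ratio, replacement rule, caliper or target population is given. The matched groups are then checked on baseline characteristics, "reporting the same statistics as previously considered to describe patients receiving SAVR and TAVR". Last comes the only 6MWT model in the article, a GEE that "will be estimated on matched data to determine the time effect on the 6MWT performance in both treatment groups", with further confounders included. No 6MWT model on the full cohort is named.

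Under Sample Size, the primary endpoint is the 6MWT gain over the first 6 months. The planned enrolment is 340 patients, 170 per group.

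**The concern.** Two questions are asked of the 6MWT: how each group recovers, and how the two groups differ. Confounding threatens the second, and matching is a reasonable answer to it. The first is descriptive. It concerns the patients who actually receive each procedure and needs no matching. The plan nevertheless assigns the time effect within each group to the matched data.

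If matching changes the case mix of a group, the modelled curve and 6-month gain for that group belong to the altered mix. A reader would naturally take them as the recovery of SAVR or TAVR patients in general, and might use them in that sense when advising patients.

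**Working it through.** **Inputs from the article.** 154 evaluable patients per group, 10% dropout, 170 enrolled per group and 340 in total (Sample Size); one GEE on matched data (Statistical Analysis).

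**Step 1: the plan's own figure.** 154 × 1.10 = 169.4, rounded up to 170; 2 × 170 = 340. This reproduces the stated enrolment. (Dividing instead, 154 / 0.9 = 171.1, gives 172 per group and 344 in total; the difference does not matter here.) What matters is that the groups are planned equal, with no surplus in either group to select matches from.

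**Step 2: why better balance must move a group.** For any baseline score, let T and S be the full-group means for TAVR and SAVR, and T* and S* the means after matching (weighted if patients are reused). Write d = T − S for the imbalance before matching and r = T* − S* for what is left. Then

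(T − T*) + (S* − S) = d − r.

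The two shifts add up to exactly the imbalance removed, whatever the algorithm. If matching improves balance, at least one group's mean has moved away from its full-group value. Three cases show how the total can be split:

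- 1:1 without replacement or caliper, equal groups: everyone is kept, both shifts are 0, r = d, and nothing is gained in balance.
- One group kept whole, the other reused or reweighted: the first shift is 0 and the other group carries all of d − r.
- Caliper matching that drops patients from both groups: the shift is shared.

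The article does not say which case applies.

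**Step 3: illustration of size.** Assumptions, none of them in the article: one normally distributed baseline score, 154 per group, greedy 1:1 matching without replacement, caliper 0.2 SD, 200 simulated data sets per row.

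| Imbalance d (SD) | Pairs kept | Share of 154 | Shift in TAVR mean (SD) | Shift in SAVR mean (SD) |
|---|---|---|---|---|
| 0.25 | 131 | 85% | −0.12 | +0.13 |
| 0.5 | 120 | 78% | −0.24 | +0.25 |
| 1.0 | 94 | 61% | −0.48 | +0.50 |
| 1.5 | 69 | 45% | −0.75 | +0.75 |

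The absolute shifts add up to nearly d in each row (for example 0.48 + 0.50 = 0.98 for d = 1.0), as Step 2 requires. The signs reflect only that TAVR was given the higher score in the simulation.

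**Step 4: from baseline score to 6MWT gain.** A shift in case mix alters the 6-month gain only if the score predicts the change in 6MWT; predicting its level is not enough. The Introduction makes this plausible, since it reports that disease severity is the main influence on functional change after valve replacement. The article gives no figure for metres of gain per SD, so no value in metres follows.

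**Step 5: planned outputs against the two aims.** The matched GEE answers the comparison. For recovery in all patients having a procedure, the article offers only medians, percentages and two-group tests. These do not model change over time, and the text does not say whether they cover the 6MWT at follow-up visits.

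**The case against.** The strongest reply is that comparing non-randomised groups on matched data is legitimate, that the study is sized on the SAVR-TAVR difference, and that a journal article need not list every supplementary analysis. The full protocol or a SAP, neither of which is shown, may contain an unmatched fit. It can be added that the planned medians and interquartile ranges are not restricted to baseline, so some full-cohort description of the 6MWT may already be intended. The counselling remark is a hope expressed in the Discussion, not an objective.

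Most of this stands as a limit on the point. The matched contrast is not criticised, and the counselling remark is only supporting context. It does not remove the point, because the article does more than leave out an unmatched model: it assigns the within-group time effect to the matched data, while its objective names both assessing and comparing. Elsewhere it does specify the full set, since the device validation is to involve all enrolled patients.

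A reader might go further and infer that both curves describe only the region of overlap, that matching keeps the fitter TAVR and the less fit SAVR patients, that the two curves are therefore displaced in opposite directions and fit neither procedure's population, and that the displacement amounts to a certain number of metres. The article does not support this. It fixes no matching rule, and one group may be kept whole. It does not say which group is fitter, and the shared eligibility criteria (age 75-90, no walking aids, isolated procedure) may narrow the difference.

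**Conclusion.** The point holds in a limited form. As written, the plan estimates each group's 6MWT time effect on matched data only, while one of its stated aims concerns all patients undergoing each procedure. With equal planned groups, any gain in balance means that at least one group's modelled curve no longer represents everyone who received that procedure. This follows from the arithmetic in Step 2 and depends on no assumption about the algorithm. That the 6-month gain shifts as well requires the balanced characteristics to predict change in 6MWT.

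The size and direction of the effect on the 6MWT cannot be determined from the article. The illustrative shifts, about 0.12 SD of a baseline score at a 0.25 SD imbalance and about 0.5 SD at 1.0 SD, rest on assumed 1:1 caliper matching; other rules would split or weight the shift differently. The SAVR-TAVR contrast is unaffected. This is an inexpensive improvement that should be made, not a flaw that undermines the study.

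**What to change.** Assign the two tasks to two fits of the same model:

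1. Keep the GEE on matched data for the SAVR-TAVR contrast, and label any curves from it as describing the matched sample.
2. Fit the GEE to all enrolled patients without matching, with procedure-by-visit terms. Report each group's 6MWT recovery curve and 6-month gain from this fit as the descriptive result. If the confounders stay in the model, average each curve over that procedure's own patients, so that it is not evaluated at a common covariate profile.

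Add a sentence saying that the unmatched curves must not be read as a causal comparison of the procedures.

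The cost is one more model run, a short addition to Statistical Analysis and a second, clearly labelled set of curves. No new data are needed and the stated sample size does not change. The Results section reports 20 patients enrolled as of October 2020, so at that stage the change could still be prespecified early.
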